**Table 1 T1:**
[figure not shown]
Data collection schedule.

### Outcome measures

2.5

#### Primary outcomes

2.5.1

##### QoL

2.5.1.1

Changes in S-IADL, Barthel-ADL, NPI-Q, and S-GDpS scores from baseline to 4 and 8 weeks after the baseline will be used to evaluate effectiveness in terms of QoL.

The S-IADL consists of 15 questions scored from 0 to 3, wherein higher scores indicate more disability in ADL. The questionnaire evaluates current and potential performance separately.^[27]^

The Barthel-ADL is widely used to evaluate ADL because it requires a short time and is easy to score.^[32]^ There are various modifications of the test, including one by Collin et al^[33]^, who simplified the scoring system to range from 1 to 20. The Korean version of the Barthel-ADL has been shown to be valid and reliable.^[29]^

The NPI-Q is used to measure abnormal behaviors. It is read and evaluated by caregivers. The questionnaire can be easily used in the medical field in the real world.^[28]^ The official Korean version of the NPI-Q is used in this study. This version is distributed by the Mapi Research Trust (https://eprovide.mapi-trust.org).

The S-GDpS is used to evaluate the symptoms of depressive mood in elderly individuals. It consists of 15 questions. The Korean version of the S-GDpS is used in this study.^[26]^

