##### Cognitive function

2.5.1.2

Changes in the MoCA-K, MMSE, CDR, and GDS scores from baseline to 8 weeks will be used to evaluate effectiveness in terms of improvement in cognitive function.

The MoCA was created to screen for individuals with MCI, who have normal scores on the MMSE. The questionnaire consists of visuospatial/executive ability, naming, memory, attention, language, abstraction, delayed recall, and orientation domains.^[34]^ The MoCA-K, which is a validated Korean version of the test,^[25]^ is used in this study. We have registered the study on *mocatest.org*.

The MMSE is one of the most broadly used screening tests for dementia. It was created by Folstein et al and can be completed in 5 to 15 minutes. This test has a total score of 30. It has the advantage of being useful in assessing changes over time, based on repeated measures during disease progression. This is because the test only has a small learning effect.^[35]^ The reliability and validity of the MMSE have been demonstrated in distinguishing moderate and severe dementia.^[24]^ The official Korean version of the test, which is supplied by the Psychological Assessment Resources, is used here.

The CDR is the most widely used test to evaluate the severity of dementia. It is divided into the following domains: memory, orientation, judgment and problem-solving, community affairs, home and hobbies, and personal care. Each category is scored on a 5-point severity scale (none, questionable, mild, moderate, and severe).^[36]^ The Korean CDR has been shown to be valid.^[16]^ The score is determined by the doctor, who makes his or her assessment based on detailed examinations of the patient and his or her caregiver.

The GDS is used to evaluate overall cognitive function. It is scored on a scale of 1 to 7 (0, no cognitive decline; 2, very mild cognitive decline; 3, mild cognitive decline; 4, moderate cognitive decline; 5, moderately severe cognitive decline; 6, severe cognitive decline; and 7, very severe cognitive decline).^[37–39]^ The validity of the Korean version of the GDS has been demonstrated.^[23]^

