### Statistical and analytical plans

2.8

Baseline characteristics and disease progression will be compared between the CT and ST groups. All continuous variables will be tested to confirm normality. Student *t* tests or Wilcoxon rank sum tests will then be used to compare the means of the 2 groups. Categorical data will be analyzed using *χ*^2^ or Fisher exact tests. Per-protocol and intention-to-treat (ITT) analyses will be used to assess all effectiveness and cost-effectiveness data. Missing volume, pattern, and mechanisms will be analyzed before the ITT analysis. If the missing mechanism is identified as missing completely at random or missing at random, as defined by Rubin,^[43]^ the multiple imputation method will be used to replicate the missing data. Scores on the S-IADL, Barthel-ADL, S-GDpS, NPI-Q, MoCA-K, MMSE, CDR, GDS, and QoL as measured by the EQ-5D and EQ-VAS, and the use of long-term care service will be compared between the 2 groups for effectiveness analysis. Means and 95% confidence intervals for continuous variables and frequencies and percentages for categorical variables will also be calculated. All statistical analyses will be performed using 2-tailed tests at a significance level of .05. In the economic evaluation, the ICER results will be analyzed deterministically using mean values, and the statistical significance of differences in ICER will be determined using the bootstrapping method. CEAC will also be analyzed and reported along with the meaningful ranges for the national thresholds. Stata MP version 14 (StataCorp LLC, TX) and SAS version 9.4 (SAS Institute Inc., Cary, NC) will be used for all of the aformentioned analyses.

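### Week-4 and week-8 QoL changes are both primary with no deciding visit, and self-selected groups are compared only by unadjusted two-sample tests

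*Protocol article*

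**What the plan says.** Section 2.5.1.1, under primary outcomes, states that changes in four scales (S-IADL, Barthel-ADL, NPI-Q, S-GDpS) "from baseline to 4 and 8 weeks after the baseline will be used to evaluate effectiveness in terms of QoL". Nothing there says whether week 4 or week 8 decides. Section 2.5.1.2 treats the cognitive scales differently, with one time point: "Changes in the MoCA-K, MMSE, CDR, and GDS scores from baseline to 8 weeks will be used to evaluate effectiveness".

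Section 2.8 names the between-group method. "Baseline characteristics and disease progression will be compared between the CT and ST groups", and for continuous variables Student t "tests or Wilcoxon rank sum tests will then be used to compare the means of the 2 groups", after a normality check. The level is the same throughout: "All statistical analyses will be performed using 2-tailed tests at a significance level of .05". For missing values under MCAR or MAR, "the multiple imputation method will be used to replicate the missing data". The section names no covariates, no model across visits, no summary over visits and no rule for several primary tests.

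Section 2.6 leaves the choice of treatment to patient and practitioner and lets it change at any time. The groups are therefore self-selected.

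**The concern.** Two things follow from reading sections 2.5.1.1 and 2.8 together.

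First, a two-sample test applied to changes at two visits, with no summary named, yields two results per scale. If they disagree, the plan does not say which one stands. If they are read so that either may count, each scale has two chances of a false positive.

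Second, the comparison uses raw changes in groups that nobody allocated. Section 2.2.1 admits patients from MCI through to dementia with a global CDR of 0.5 to 2.0, so the groups may well start at different levels. Section 2.8 compares baseline characteristics but attaches no consequence to a difference. A baseline gap can then pass into the change comparison, and the variance that the baseline score could explain stays in the error term.

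**Working it through.** **No stated figure to reproduce.** The article gives no effect size, SD, correlation or power. Its one calculation, 120/(1 − 0.20) = 150 in section 2.7, reproduces but does not bear on this point.

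**Number of tests.** From 2.5.1.1: 4 scales × 2 visits = 8 primary QoL tests. From 2.5.1.2: 4 scales × 1 visit = 4 more, so 12 in all.

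**Error rate per QoL scale if either visit may count.** Two two-sided tests at .05 (section 2.8). If independent: 1 − 0.95² = 0.0975. If the two changes are correlated, the bivariate normal probability that at least one exceeds 1.96 in absolute value is:

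| Correlation of the two changes (assumed) | P(at least one false positive) |
|---|---|
| 0 | 0.0975 |
| 0.5 | 0.091 |
| 0.7 | 0.084 |
| 0.9 | 0.070 |

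Under compound symmetry with visit correlation r, the two changes share the baseline score. Their covariance is 1 − r and each variance is 2(1 − r), so their correlation is 0.5 whatever r is. That gives about 9%; the other rows allow for departures.

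**Variance of the week-8 comparison.** Assumptions: equal SD of 1 at each visit, compound symmetry, complete data.

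- Raw change: 2(1 − r)
- Adjusted for baseline score: 1 − r²
- Ratio: (1 − r²)/[2(1 − r)] = (1 + r)/2, a reduction of (1 − r)/2

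| r | Raw change | Baseline-adjusted | Reduction |
|---|---|---|---|
| 0.5 | 1.00 | 0.75 | 25% |
| 0.7 | 0.60 | 0.51 | 15% |
| 0.9 | 0.20 | 0.19 | 5% |

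**Illustration of the baseline gap.** Assumptions: the groups differ by d = 0.3 SD at baseline, both regress toward a common mean, and there are 60 per group (half of the 120 complete patients targeted in section 2.7). The spurious difference in change is (1 − r)d, and its standard error is √[2(1 − r)] × √(2/60).

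- r = 0.5: 0.15/0.183 = 0.8 standard errors, so a nominal 5% test rejects about 13% of the time.
- r = 0.7: 0.09/0.141 = 0.6 standard errors, about 10%.

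The size depends on d, and the direction depends on the common-mean assumption.

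**The case against.** The strongest reply is that a condensed article need not give the model, and that visit hierarchy commonly belongs in an analysis plan that is not shown. The word for separate testing also appears nowhere in section 2.8; testing visit by visit is an inference from the named tests. What stands against this is that section 2.8 does name the test for the effectiveness comparison. The point concerns a stated method, and a later plan with an adjusted longitudinal model would depart from it.

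Other objections hold in part:

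- A two-sample test of change at one visit is valid for that visit. Leaving out the other visit neither biases it nor raises its own error rate. The defect is the absence of a deciding result and of adjustment.
- In non-randomised groups, change-score and baseline-adjusted analyses answer different questions and can disagree (Lord's paradox). If each group regresses to its own mean, the illustration above does not apply. This limits the bias claim, but it does not make a comparison with no confounders preferable.
- Multiple imputation already keeps patients with only one follow-up visit, so retaining them is not a new benefit of a mixed model.
- The scales are bounded, and section 2.8 has a rank-based fallback that a Gaussian model alone would lose.

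Two stronger readings are tempting. A reader might infer that the plan throws away 40–50% of the attainable precision by not pooling visits. That reduction, from (1 + r)/2 − r² against 2(1 − r) at r = 0.7 and 0.5, belongs to a baseline-adjusted average of weeks 4 and 8 with a similar effect at both. The article names no such average, and a week-8 contrast does not obtain it. A reader might also infer a 34% chance of a false QoL claim from 1 − 0.95⁸ = 0.337. This assumes independent scales and that any one success suffices; the article states neither.

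**Conclusion.** The point holds in a limited form and should be acted on. The plan has eight primary QoL tests with no deciding visit, and it compares self-selected groups without adjustment.

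The ambiguity raises the error rate per scale to about 7–10% only if either visit may count; with one visit named it is 5%. The precision gained at week 8 from baseline adjustment is modest, about 25% of the variance at r = 0.5 and only 5% at r = 0.9. These figures rest on assumed correlations, compound symmetry and complete data.

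The exposure to baseline differences matters more than the lost precision, but its size cannot be fixed from the article. The visit ambiguity concerns only the four QoL scales; the lack of adjustment also affects the cognitive scales.

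**What to change.** In section 2.8:

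1. Analyse each QoL scale in one repeated-measures model with baseline score, group, visit, group-by-visit, hospital and collected confounders such as diagnosis (MCI or dementia), baseline CDR, age, sex and education.
2. Name the week-8 contrast as deciding for each scale and week 4 as supportive. The model alone does not settle this; the named contrast does.
3. Combine the model with the planned multiple imputation.
4. Keep a rank-based or bootstrap sensitivity analysis for skewed or bounded scores.
5. State that adjustment reduces confounding by measured variables and does not remove it, and word the result that way.

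The cost is a change of wording, slightly more analysis work and reliance on model assumptions. No new data are needed, and both packages named in section 2.8 can fit such a model. The wording should be fixed before outcome data are examined, so that the deciding visit cannot be chosen afterwards.

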##### Cognitive function

2.5.1.2

Changes in the MoCA-K, MMSE, CDR, and GDS scores from baseline to 8 weeks will be used to evaluate effectiveness in terms of improvement in cognitive function.

The MoCA was created to screen for individuals with MCI, who have normal scores on the MMSE. The questionnaire consists of visuospatial/executive ability, naming, memory, attention, language, abstraction, delayed recall, and orientation domains.^[34]^ The MoCA-K, which is a validated Korean version of the test,^[25]^ is used in this study. We have registered the study on *mocatest.org*.

The MMSE is one of the most broadly used screening tests for dementia. It was created by Folstein et al and can be completed in 5 to 15 minutes. This test has a total score of 30. It has the advantage of being useful in assessing changes over time, based on repeated measures during disease progression. This is because the test only has a small learning effect.^[35]^ The reliability and validity of the MMSE have been demonstrated in distinguishing moderate and severe dementia.^[24]^ The official Korean version of the test, which is supplied by the Psychological Assessment Resources, is used here.

The CDR is the most widely used test to evaluate the severity of dementia. It is divided into the following domains: memory, orientation, judgment and problem-solving, community affairs, home and hobbies, and personal care. Each category is scored on a 5-point severity scale (none, questionable, mild, moderate, and severe).^[36]^ The Korean CDR has been shown to be valid.^[16]^ The score is determined by the doctor, who makes his or her assessment based on detailed examinations of the patient and his or her caregiver.

The GDS is used to evaluate overall cognitive function. It is scored on a scale of 1 to 7 (0, no cognitive decline; 2, very mild cognitive decline; 3, mild cognitive decline; 4, moderate cognitive decline; 5, moderately severe cognitive decline; 6, severe cognitive decline; and 7, very severe cognitive decline).^[37–39]^ The validity of the Korean version of the GDS has been demonstrated.^[23]^

##### Others

2.5.1.3

“Long-term care score” and “use of long-term care service” will be investigated at baseline and 12 weeks after the baseline. The “use of long-term care service” includes home-visit care, home-visit bathing, home-visit nursing, day and night care, short-term care, and use of geriatric care facilities.

#### Secondary outcomes

2.5.2

The secondary outcomes in our study comprise cost-effectiveness analysis measurements. Cost components such as direct medical costs, and direct nonmedical costs will be measured using case report forms and hospital administrative data. The preference-based health utility measure instrument of the EQ-5D-5L will be calculated as quality-adjusted life years using the area under the curve method.^[40]^ The incremental cost-effectiveness ratio (ICER),^[41]^ the confidence interval of the ICER, and the cost-effectiveness acceptability curve (CEAC)^[42]^ will also be analyzed to evaluate the significance of the cost-effective outcomes in South Korea. The schedule for data collection can be found in Table 1.

### Treatments

2.6

The participants receive treatment for MCI/dementia, mostly based on their practitioners’ clinical opinions; thus, there is no fixed treatment for the study. The participants can freely choose any type of WM and/or KM treatment method. When a participant wishes to receive both WM and KM treatment, the practitioner of 1 type of medicine used for the patient's treatment will make a “request for a collaborative treatment” to a practitioner of the other type of medicine. The participants can freely decide the type of treatment in consultation with their practitioners at any time, as with general care. All treatments that the participants receive will be recorded and monitored.

### Rationale for sample size

2.7

The aim of this study is to collect complete data from 120 patients assuming adequate recruitment during the study period. Estimating a 20% missing data rate, a minimum of 150 patients should be enrolled. Thus, considering the inherent characteristics of a prospective observational study, 180 participants will be recruited to collect sufficient data for statistical analysis and interpretation.

### Statistical and analytical plans

2.8

Baseline characteristics and disease progression will be compared between the CT and ST groups. All continuous variables will be tested to confirm normality. Student *t* tests or Wilcoxon rank sum tests will then be used to compare the means of the 2 groups. Categorical data will be analyzed using *χ*^2^ or Fisher exact tests. Per-protocol and intention-to-treat (ITT) analyses will be used to assess all effectiveness and cost-effectiveness data. Missing volume, pattern, and mechanisms will be analyzed before the ITT analysis. If the missing mechanism is identified as missing completely at random or missing at random, as defined by Rubin,^[43]^ the multiple imputation method will be used to replicate the missing data. Scores on the S-IADL, Barthel-ADL, S-GDpS, NPI-Q, MoCA-K, MMSE, CDR, GDS, and QoL as measured by the EQ-5D and EQ-VAS, and the use of long-term care service will be compared between the 2 groups for effectiveness analysis. Means and 95% confidence intervals for continuous variables and frequencies and percentages for categorical variables will also be calculated. All statistical analyses will be performed using 2-tailed tests at a significance level of .05. In the economic evaluation, the ICER results will be analyzed deterministically using mean values, and the statistical significance of differences in ICER will be determined using the bootstrapping method. CEAC will also be analyzed and reported along with the meaningful ranges for the national thresholds. Stata MP version 14 (StataCorp LLC, TX) and SAS version 9.4 (SAS Institute Inc., Cary, NC) will be used for all of the aformentioned analyses.

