### Study design and setting

2.1

A multicenter, outpatient department (OPD)-based, prospective observational study of patients diagnosed with MCI or dementia is being conducted from April 2018 to December 2018, as a part of a Registry for Korean Medicine and Western Medicine Collaborative Treatment (REKOMENT study). Participants are recruited from 6 university-affiliated hospitals and 1 national medical center, which are participating in the “second-stage pilot project of KM-WM collaborative treatments.” The participants receive treatments from practitioners of KM and/or WM as they would in the real world, and are asked to undergo additional assessments. We will analyze the type of treatment (collaborative or sole treatment), changes in assessment scores, and costs for treatment of MCI/dementia. A comparative observational study design has been adopted to compare the participants in a collaborative treatment (CT) group and those in a sole treatment (ST) group. The study flowchart can be found in the flow diagram (Fig. 1).

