### Data sources, measurements, and management

2.4

Data regarding effectiveness will be collected using participant surveys and clinical evaluations. Data regarding costs will be obtained using participant surveys, administrative data from each institution, and Health Insurance Review and Assessment (HIRA) data.

The participant survey includes information regarding demographic characteristics, medical history, use of long-term care services, and costs for the MCI/dementia treatments. The demographic information obtained includes date of birth, sex, level of education, and occupation (current or past). The medical history information collected includes treatment history, other diseases that the patient has, history of drinking and smoking, and family history.

The Korean Medical Pattern Identification for Dementia (KPD) score will be used to assess pattern identification in each patient.^[21]^ Pattern identification is also known as syndrome diagnosis, and is a major method used to classify symptoms. It is broadly used in traditional Chinese medicine and KM. Information regarding long-term care services will also be obtained, including the score of long-term care insurance service and the contents of long-term care service currently in use. Direct medical costs and direct nonmedical costs of the MCI/dementia treatments will be assessed using surveys of patients or their guardians based on the “limited societal perspective.”^[22]^

The clinical evaluation includes: assessment of the severity of MCI/dementia using measures such as the CDR,^[16]^ Global Deterioration Scale (GDS),^[23]^ Mini-Mental State Exam (MMSE),^[24]^ Korean Montreal Cognitive Assessment (MoCA-K),^[25]^ and Short-Form Geriatric Depression Scale (S-GDpS);^[26]^ and 2) assessment of QoL using measures such as the Seoul Instrumental Activities of Daily Living (S-IADL),^[27]^ Neuropsychiatric Inventory-Questionnaire (NPI-Q),^[28]^ Barthel Activities of Daily Living (Barthel-ADL),^[29]^ EuroQoL-5 Dimension (EQ-5D),^[30]^ and EuroQol-visual analog scale (EQ-VAS).^[31]^

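### Collaborative and sole treatment groups are formed by choice, but the comparison tests named in section 2.8 are unadjusted, so prognostic differences can be read as an effect of collaboration

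*Protocol article*

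**What the plan says.** Section 2.1 sets out a non-randomised comparison: "A comparative observational study design has been adopted to compare the participants in a collaborative treatment (CT) group and those in a sole treatment (ST)". Section 2.6 describes how patients come to be in a group: "The participants can freely choose any type of WM and/or KM treatment method". Treatment is "mostly based on their practitioners’ clinical opinions; thus, there is no fixed treatment for the study", and the choice stays open: "The participants can freely decide the type of treatment in consultation with their practitioners at any time, as with general care".

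Section 2.8 gives the comparison. It begins: "Baseline characteristics and disease progression will be compared between the CT and ST groups". Continuous variables are checked for normality, after which Student t or "Wilcoxon rank sum tests will then be used to compare the means of the 2 groups". Categorical data go to chi-square or Fisher exact tests. The scale scores, EQ-5D, EQ-VAS and use of long-term care are then compared between the two groups as the effectiveness analysis. The ICER is computed from mean values, with bootstrapping for its uncertainty.

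Sections 2.5.1.1 and 2.5.1.2 define the scale outcomes as changes from baseline. Section 2.4 shows that date of birth, sex, education, occupation, medical and treatment history, and baseline severity are all recorded.

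**The concern.** The introduction asks whether collaborative treatment is more effective and more cost-effective than either system alone. That is a causal comparison between groups that patients and practitioners form themselves. The sample mixes MCI and dementia over a global CDR of 0.5 to 2.0, so prognosis varies, and those choosing treatment can see much of what drives it.

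The tests named in section 2.8 are the usual ones for randomised groups. Baseline characteristics are compared, but the article describes no later step that uses the result. It mentions no regression, matching, weighting or stratification. The limitations in the Discussion cover the outpatient setting, the selected institutions and the short follow-up, but not confounding. If the analysis follows this text, a difference in the kind of patient who seeks both systems can appear as a benefit or harm of collaboration, in both the effectiveness and the economic results.

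**Working it through.** **The plan's own figure.** Section 2.7 aims for 120 complete cases with 20% missing: 120 / (1 − 0.20) = 150, as stated. The rise to 180 is a judgement with no formula. No effect size, SD, power or group ratio is given, so the inputs below on imbalance and correlation are assumptions.

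**Inputs.** Two-sided alpha 0.05 (section 2.8). 120 complete cases (section 2.7), split 60/60 (assumed). No true treatment effect (assumed). A baseline prognostic factor differs by m SD between groups and correlates r with the change score (both assumed).

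**Formulas.** Bias = r × m, in SD of the outcome. SE = √(1/n₁ + 1/n₂). Rejection rate = P(|Z + bias/SE| > 1.96).

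**Results for change scores, r = 0.4.** SE = √(1/60 + 1/60) = 0.183.

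| Imbalance m | Bias | Bias/SE | Rejection rate |
|---|---|---|---|
| 0.2 SD | 0.08 SD | 0.44 | 7.2% |
| 0.4 SD | 0.16 SD | 0.88 | 14.2% |

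With a 90/30 split, SE = √(1/90 + 1/30) = 0.211, and m = 0.4 gives 11.8%.

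**More patients do not help.** For m = 0.3 and r = 0.5 (bias 0.15 SD), the rate is 13.0% at 60/60 and 17.2% at 90/90. The bias stays the same while the SE shrinks.

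**Does the choice of test matter, and does adjustment work?** Simulation with 60 per group, 3,000 runs per setting and no true effect:

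| m, r | t test | Wilcoxon | Adjusted for the factor |
|---|---|---|---|
| 0.3, 0.3 | 8.6% | 8.3% | 5.7% |
| 0.3, 0.5 | 13.1% | 12.6% | 4.6% |

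The normality check therefore gives no protection, because both tests carry the same bias. Adjustment for the measured factor brings the rate back to about 5%.

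**If raw follow-up scores were compared instead.** With r = 0.8 between baseline and follow-up and m = 0.4, the bias is 0.32 SD, bias/SE = 1.75, and the rejection rate is about 42%. This shows why section 2.8, which speaks of scores, should be aligned with section 2.5.1, which defines changes. It is not the expected size of the problem.

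**The case against.** The strongest reply is that a journal article condenses the plan, and covariate models may sit in an analysis plan not shown. That stands in part: section 2.8 does not say its tests are the only ones, and silence on later use of the baseline comparison does not prove that nothing is done. But the article assigns the effectiveness comparison to named tests. An adjusted main analysis would have to depart from that text, not merely fill it in.

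A second reply is that change scores already deal with baseline differences. They remove a fixed gap in starting level. They do not remove different expected courses by diagnosis, severity, age, education or prior treatment, nor regression to the mean.

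Several stronger readings are tempting, and the documents do not support them:

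- *Error near 42%.* This needs raw follow-up scores to be compared. Section 2.1 refers to changes in scores, section 2.5.1 defines changes, and section 2.8 itself mentions disease progression.
- *Baseline differences will be mistaken for an effect.* No imbalance is documented, so only that they can be.
- *Group choice is driven by severity, education or income.* No such association is reported, and income is not among the demographic items listed in section 2.4.
- *Group and hospital are linked.* Five of the seven institutions in section 2.9 are Korean-medicine or oriental hospitals by name. That might bear on KM versus WM, but ST contains either system alone, and every site belongs to the collaborative pilot. A link with CT versus ST is speculation.
- *The rank-sum test cannot be adjusted.* Stratified and ordinal-model counterparts exist. The test named here is simply unadjusted.

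**Conclusion.** The point holds. The stated CT-versus-ST tests make no allowance for self-selection, and neither does the stated ICER calculation, although the study's aim is comparative. Under the plan's own change-score outcomes, the illustrative type I error is about 7% to 14% instead of 5%. That range rests on assumed values: no true effect, 60/60 complete cases, a 0.2 to 0.4 SD imbalance and a correlation of 0.4 with change. The true size could be smaller or larger, and its direction is unknown. The weakness itself does not depend on those figures. It affects every effectiveness comparison and carries into the economic evaluation, so it should be corrected before analysis.

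**What to change.** - Make the main CT-versus-ST comparison one pre-specified adjusted analysis per outcome: either regression of the change score with robust standard errors, or propensity-score overlap weighting.
- Use a short list of baseline covariates already collected: the outcome's baseline value, diagnosis or CDR (not both where they overlap), age, sex, education, treatment history and hospital.
- For sparse binary outcomes, which use of long-term care services may prove to be, use weighting or a reduced model.
- Apply the same adjustment to costs and QALYs, inside each bootstrap sample.
- State in section 2.8 that changes from baseline are analysed for the scale outcomes, to match section 2.5.1.
- Report standardised mean differences before and after adjustment, keep the unadjusted tests as descriptive, and add residual confounding to the limitations.

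**Cost.** Wording and modest programming, with no new data. If each of the six non-hospital covariates takes one degree of freedom and seven hospitals take six, the model spends 6 + 6 = 12 besides the treatment term, from about 120 complete cases. Multi-level covariates would cost more, so the list must stay short. Unmeasured confounding remains, and baseline adjustment does not handle later changes of treatment type, which section 2.6 allows.
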